#### Intervention Delivery

All participants will receive individual in-person training on how to use the mobile app in order to minimize possible errors of manipulation. Participants will be advised to use the EMMA app as desired to complete the EMMA intervention (8-week web-based program). Furthermore, participants will be asked to complete the daily diary in the app, assessing pain levels and psychological symptoms including mood, stress, thoughts, behaviors, and activities 3 times per day for 2 weeks before the intervention and 2 weeks after the EMMA intervention in line with other ecological momentary assessment protocols in chronic pain research [49]. Participants will receive an alarm 3 times a day (morning, afternoon and evening) at times determined by the participant, with the requirement that the chosen times be at least 3 hours apart and at least 3 hours after awakening in the morning to allow adequate sampling of variables across the course of the day. Each log will be date- and time-stamped in the app. Studies [50] of participants using electronic devices typically show high rates of adherence at the time of the scheduled prompts; in clinical populations, 85% or more of prompts were answered. We will inform the participants (during the coaching session for the use of the app) about the importance of regularly entering data; participants with less than 50% of data entries will be excluded from analysis. We will continuously monitor the participants on the regularity of their responses to the prompts, and in case of nonadherence, we will contact them and remind them about the importance of entering the data regularly.

The Pain Coping Strategies Questionnaire [59] is one of the most widely used measures for pain coping and catastrophizing. Measures derived from the Pain Coping Strategies Questionnaire have been shown to be associated with various measures of functioning among patients with different pain conditions [60-62]. The Pain Coping Strategies Questionnaire has demonstrated reliability and validity in several samples of older adults, including those who are older than 75 [63].

#### Usability and Acceptability

After the trial period, participants will complete questionnaires to evaluate the usability and acceptability of the EMMA intervention in healthy older adults, using the Technology Acceptance Model [64] and its version adapted for older adults [65], System Usability Scale [66], and the Emotional Metric Outcomes scale [66]. In addition, all participants will be invited to take part in a semistructured telephone interview at the end of the intervention period. The semistructured interview will focus on evaluating the acceptability of the intervention. Participants will specifically be asked about patterns of app use, including frequency and timing, and their experiences, attitudes, and perspectives on integrating the EMMA intervention into their pain self-management strategies. Participants’ perceptions of the barriers to and facilitators of use of the intervention will be explored. The interviews will be audiorecorded and transcribed verbatim for analysis.

#### Statistical Analysis

We will utilize SPSS software (version 27 or higher; IBM Corp) for management and analysis of data and the latest version of HLM for the Ecological monitoring data (version 8; Scientific Software International Inc). Before analysis, all outcome variables will be tested for normality using the Kolmogorov-Smirnov test and, if necessary, transformed to obtain a normal distribution. Differences in variables (demographic, diagnostic, pain-related) will be compared using *t* tests for continuous variables and chi-square tests for categorical variables. For the primary and secondary outcomes, participants self-reported pain disability, pain severity and impact of pain on daily function, depression, anxiety, quality of life, and pain coping strategies will be compared before and after the intervention. Data from the pain diary yield intensive longitudinal data that are clustered as they represent series of measurements that stem from different individuals. in keeping with current consensus [67] on how to analyze experience sampling data, we will use a multilevel approach to analyze these data, which takes into account clustering and provides flexible tools to investigate within-subject phenomena, such as responses to stressors or pain shifts. We will use software (the latest version of HLM software) that allows for simultaneous within-subject and between-subject modeling, examination of associations among individual difference variables, and examination of individual differences within-subject parameters. In line with similar studies [42], we will use an inductive thematic content analysis for the qualitative interviews. Transcribed interviews will be read and reread to promote immersion in the data and close examination of the interview content. Preliminary themes and subthemes will be generated and continually refined.

## Results

The study is currently ongoing. Development of the digital pain diary has started. Psychotherapeutic web-based app content has been digitalized. Recruitment of participants for the co-design workshops will start as soon as we have a functioning prototype of the electronic pain diary and EMMA intervention, which is to be expected in September 2021. The feasibility study will start as soon as the co-design process is finished and all required changes have been implemented into the pain diary and the EMMA intervention. We expect to start the feasibility study at the beginning of 2022.

## Discussion

### General

This article describes a research protocol for a development and feasibility study of a web-based psychological intervention for older people with chronic pain to support pain self-management. We will develop a self-guided web-based program for chronic pain that consists of an electronic pain diary and a web-based smartphone app with psychotherapeutic treatment modules that will be tested for feasibility as well as providing the first indicators of efficacy. The EMMA intervention combines a strong body of evidence using cognitive behavioral intervention designs with contemporary mHealth principles, allowing for the intervention to be used when and where it matters the most. Potential benefits for older adults with chronic pain are invaluable as this app will address most barriers for effective treatment of older people with chronic pain. This feasibility study should provide information for further optimization of the intervention, and if successful, this app will be tested in an RCT and could become a model to address the needs of older people with chronic pain in Switzerland.

We believe that developing an web-based self-management tool for pain that is suited for older adults will address a major gap for the treatment of pain in older adults. This system could serve as a tailored and customized education tool for individualized services and as a social support and social engagement tool for enhanced pain management. Furthermore, this system could be a potential method of communicating more effectively with health care providers, with the caveat that providers might not have adequate time. Relaying real-time pain status to providers may provide a support tool for patients to convey the daily pain status to their social network and prompt their network for motivation and coping strategies. Furthermore, we also aim to empowering users with this system by supporting them in actively managing their own condition, at their convenience, by self-monitoring to develop a set of self-management strategies.

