**Methods:**

The key clinical and engagement features of the intervention were established through the integration of evidence-based material from cognitive behavioral therapy for the treatment of chronic pain in older adults. The development process uses a co-design approach and actively involves end-users in the design process by incorporating feedback from focus groups with older adults in order to inform a user-centered intervention design. For the co-design process, we will include 10 older adults with chronic pain, who will discuss the requirements for the app in workshops in order to ensure suitability of the app for older adults with chronic pain. In order to test the feasibility and acceptability of the intervention, we will include a sample of 30 older adults with chronic pain who will test all features of the intervention for a period of 8 consecutive weeks. After the trial period, validated instruments will be used to assess usability and acceptability, as well as influence on pain levels and associated physical and psychological symptoms. Participants will be invited to take part in a semistructured telephone interviews after the trial period to explore their experiences using the app.

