### Feasibility Study

#### Study Purpose and Specific Aims

Feasibility studies are carried out prior to a main study to estimate important parameters required to design the main study, whereas a pilot study is a smaller version of the main study carried out to evaluate if all of the components of the main study can work together [41]. The primary goal of this study is to evaluate the feasibility, usability, and acceptability of the EMMA intervention in a sample of older adults with chronic pain. Because this is a feasibility study, a sample size calculation is not appropriate. However, consistent with other comparable studies [42-44], a target of 30 older adults will be used. Study protocol, intervention, participant information, and informed consent will be reviewed by the Ethics committee of the Canton Vaud, and all participants will provide written informed consent. The study will be conducted according to the principles of the 2013 Declaration of Helsinki.

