#### Screening and Diagnostic Measures

All participants will undergo the same screening procedure, including a standardized questionnaire to test the general inclusion and exclusion criteria, a structured clinical psychiatric interview for the diagnosis of mental disorder (Structural Clinical Interview for Diagnostic and Statistical Manual for Mental Health [47]), and Mini Mental State Examination [46]. The assessment will be performed by trained research assistants from the University of Fribourg and will be supervised by a senior clinician (KL). We will ask participants to provide sociodemographic data (including age, sex, education, marital status), information on their smoking, drinking, physical activity, self-perception of aging, basic and instrumental activities of daily living, and health care use associated with the pain problems in the past 3 months. Basic and instrumental activities of daily living are each measured with 7 in a modified version of the OARS Multidimensional Functional Assessment Questionnaire [48].

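### Before-after change in a single uncontrolled group is presented as a first sign of efficacy and of influence on pain, which it cannot show at any sample size

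*Protocol article*

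**What the plan says.** The Discussion (General) states that the programme will be "tested for feasibility as well as providing the first indicators of efficacy" and that an RCT follows if the study succeeds. The Abstract (Methods) says the instruments used after the trial period will assess usability and acceptability "as well as influence on pain levels and associated physical and psychological symptoms".

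The design behind these statements is a single group. The Abstract says "we will include a sample of 30 older adults with chronic pain who will test all features of the intervention"; no control group or allocation is described anywhere. Under Statistical Analysis, the primary and secondary outcomes "will be compared before and after the intervention". Study Purpose and Specific Aims gives feasibility, usability and acceptability as the primary goal, while Outcome Measures names the Pain Disability Index as the primary outcome.

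Other relevant facts:
- Participants: the criteria set no requirement for stable pain or stable treatment.
- Intervention Delivery and Operational Challenges: staff give individual training, contact people who miss entries, and offer guidance throughout.
- Screening and Diagnostic Measures: the screening battery asks about "health care use associated with the pain problems in the past 3 months". This item is not among the outcomes measured before and after.
- Limitations: these cover discomfort with technology, recruitment and non-use. The lack of a control group is not mentioned.

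**The concern.** Efficacy, and influence on pain, are contrasts with what would have happened without the app. A single group seen twice does not supply that contrast. An average improvement could come from the app, but also from regression to the mean, the natural course of pain, staff contact or other care received over the same weeks. The Introduction presents the app as self-guided, so the staff contact in this study is not simply part of the product.

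At stake is what the study may conclude. If before-after improvement is reported as a first sign of efficacy, readers and the team planning the RCT may take it as evidence of an effect. With several instruments compared in the same way, some apparent improvement can also arise by chance.

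**Working it through.** **The plan's own figure.** The only number is the target: "a target of 30 older adults will be used". It rests on comparable studies, and the article adds: "Because this is a feasibility study, a sample size calculation is not appropriate". With no alpha, power, effect size or SD given, 30 can be neither reproduced nor refuted. Everything below is illustration on assumed inputs, with two-sided alpha 0.05 per score.

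**Step 1: count the scores** (Outcome Measures). Pain Disability Index 1; Brief Pain Inventory 2 (severity and impact, listed separately under Statistical Analysis); Hospital Anxiety and Depression Scale 2; Geriatric Depression Scale 1; WHO quality of life 4 domains; coping questionnaire at least 1. Sum: 1 + 2 + 2 + 1 + 4 + 1 = 11 or more.

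**Step 2: no app effect, but a non-specific improvement.** Let d be that improvement in SD of the change score. The chance of p<0.05 in the improving direction is P(T > t(0.975, n-1)), where T is noncentral t with n-1 degrees of freedom and noncentrality d×√n. At n=30:

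| d (assumed) | P(p<0.05), one score |
|---|---|
| 0.2 | 18% |
| 0.3 | 36% |
| 0.4 | 56% |
| 0.5 | 75% |

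At n=100, d=0.3 gives 84%. A larger single arm makes a non-specific improvement more likely to look significant.

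**Step 3: how large might regression to the mean be?** Let s be the distance of entrants' mean from the population mean in baseline SD, and r the retest correlation (both assumed; equal SD at both times). Expected drift is (1-r)×s baseline SD. The SD of change is √(2(1-r)) baseline SD, so d = s×√((1-r)/2).
- r=0.9, s=0.5: d = 0.5×√0.05 = 0.11, and P(p<0.05) = 9%.
- r=0.6, s=1.0: d = 1.0×√0.20 = 0.45, and P(p<0.05) = 66%.

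**Step 4: no change at all, 11 scores.** If independent, the chance of at least one p<0.05 is 1 - 0.95^11 = 43%. This counts worsening as well; for improvement alone it is 1 - 0.975^11 = 24%. Simulating 11 equally correlated paired t tests at n=30 (10,000 runs) gives, for either direction, about 38%, 31% and 23% at correlations of 0.3, 0.5 and 0.7.

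**Step 5: precision of a descriptive report.** The 95% CI half-width is t(0.975, 29)/√30 = 2.045/5.477 = 0.37 SD of change. It covers sampling error only, not the bias from having no control.

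**The case against.** The best defence is that the claim is hedged and secondary. The stated goal is feasibility, the efficacy phrase speaks only of first indicators, and the same paragraph leaves the test to an RCT. A single arm is normal at this stage. Entry requires persistent pain but no minimum score, and recruitment is broad, so selection at a peak is not built in. A diary three times a day for 2 weeks before and after (3×14 = 42 prompts each) also gives diary pain a repeated baseline.

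Much of this stands and limits the severity. It does not supply a comparator: the diary averages out day-to-day noise but not slower fluctuation, staff contact or other care, and it does not cover the questionnaires.

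A reader might infer stronger points, which the document does not support:
- *That 30 is too few.* Nothing shows it wrong for feasibility, and more people in one arm would not help.
- *That the RCT will be sized on the observed change and so be underpowered.* The article never says this. It says only that feasibility studies estimate design parameters and that an RCT may follow.
- *That a positive finding is likely.* For the single primary outcome this depends on the assumed drift: 9% in the mildest case of Step 3, 66% in the strongest.
- *That the missing multiplicity adjustment is a fault.* The article names one primary outcome and gives no test or alpha for these comparisons; an analysis plan not shown may do so.
- *That other treatment will certainly go unrecorded.* The article lists the item only at screening; the full protocol may repeat it.

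**Conclusion.** The concern holds as one of over-stated aims. The efficacy and influence wording claims more than an uncontrolled before-after comparison can give, and the Limitations do not say so. The binding fault is the missing control, not the sample size.

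The percentages show how readily an app with no effect could appear to work. They rest on assumed drift, retest correlation, inter-score correlation and alpha, and are not predictions for this study. The single-arm feasibility design itself need not change. The point is worth correcting because it governs what may be concluded, and the correction is cheap.

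**What to change.** 1. In the Discussion (General) and the Abstract (Methods), replace the efficacy and influence wording with a statement that the study will describe before-after change.
2. Report mean change with its 95% CI as descriptive. At n=30 the half-width is about 0.37 SD of change.
3. Add to the Limitations that there is no control group, so change cannot be attributed to the app.
4. State that SDs, pre-post correlation and missingness will inform the RCT, and that the change observed here will not serve as its target difference.
5. Ask the existing 3-month item on pain-related health care use again at the final assessment, so that co-treatment can be described. If the assessments bracket the diary periods, the interval is 2 + 8 + 2 = 12 weeks, close to the item's recall period.

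The cost is a more modest claim and one repeated questionnaire item. No extra arm, participants or visits are needed.

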### Limitations

#### Discomfort With Technology

Although many older adults use mobile technologies, many do not. Moreover, those who do use these technologies often use fewer features than young adults and are easily confused by the wealth of potential apps [68]. Therefore, we will incorporate older adults in the development process to ensure that the app can be navigated easily. We will also provide brief orientation sessions for each participant, where they learn to navigate the app’s features. This process will be continued until the participant is comfortable with their ability to access and navigate the app interface. Most importantly, we aim to minimize these limitations during phase 1 by receiving and iterating on participants feedback related to the app. We will use Web Content Accessibility 2.0 guidelines to ensure to meet the needs of older people (in terms of visibility, design, and navigation). In particular, we will use a large font for text in form fields and other controls to accommodate older adults with visual impairments. Because some older adults lose contrast sensitivity, we will adapt high contrast colors will be used. For the videos, transcripts will be provided to account for eventual hearing loss, background noise, and distractions. Due to possible cognitive decline and inexperience with browsing habits, navigation, and presentation of the program, the organization of pages will be kept as simple as possible. Furthermore, pop-ups, new windows, and tabs will be limited to avoid confusion. Lastly, there will be no time restrictions to complete the transactions.

#### Operational Challenges

Conducting this study will involve several operational challenges. The first challenge is the recruitment of an adequate number of older people with chronic pain who are willing to participate. The second challenge is the nonuse of the intervention. Previous studies have shown that nonadherence is a common problem in web-based interventions [69]. To prevent nonusage, we have taken several measures. Patients will receive reminders when they have not logged into the web-based app. The app includes daily inspirational quotes and blogs to encourage daily use. In addition, log data enable us to track the amount of time patients spend using the intervention. Finally, guidance by the study personnel is offered throughout the intervention to motivate patients, answer questions, and overcome difficulties.

## Abbreviations

mHealth: mobile health
